### Clinical evaluation system

2.8

The clinical evaluation utilized PSQI, ISI, NDSI, and SF-36. As evidenced by prior studies (24–27), all instruments underwent systematic cultural adaptation and linguistic validation, and have been successfully utilized in Chinese clinical practice for years: PSQI has been widely adopted in insomnia assessment, ISI demonstrated robust validity in gastrointestinal disease research, NDSI exhibited specific discriminative capacity for dyspeptic symptoms in Chinese populations, and the Chinese version of SF-36 showed consistent reliability and validity in evaluating quality of life among elderly populations, collectively ensuring measurement reliability.

#### Baseline characteristics

2.8.1

Data were collected using a standardized Case Report Form (CRF), including:

Demographic characteristics: Sex, age, educational attainment, and occupational category.

Clinical characteristics: Disease duration (months), marital status, and dietary patterns.

Anthropometric measurements: Body mass index (BMI, kg/m^2^).

#### Primary outcome measures

2.8.2

##### Pittsburgh sleep quality index (PSQI)

2.8.2.1

Assessment timepoints: Baseline (T0), post-intervention (T1, week 3), and follow-up (T2, week 4 post-treatment).

Evaluation domains: Seven components including subjective sleep quality, sleep latency, and sleep duration.

Scoring system: Total scores range from 0 to 21, with ≥8 indicating sleep disturbance. A change ≥3 points was considered clinically significant.

##### Nepean dyspepsia symptom index (NDSI)

2.8.2.2

Assessment timepoints: Consistent with the aforementioned schedule (T0-T2).

Symptom assessment: Four core symptoms (early satiety, postprandial fullness, etc.) were quantified according to Rome IV criteria.

Scoring system: Each item was scored 0–4 (total range 0–16). A symptom reduction rate ≥ 30% indicated clinical effectiveness.

#### Secondary outcome measures

2.8.3

##### Insomnia severity index (ISI)

2.8.3.1

Assessment timepoints: Consistent with the aforementioned schedule (T0-T2).

Multidimensional assessment: Five clinical dimensions were evaluated, including sleep disturbance severity and daytime functional impairment.

Clinical thresholds: 0–7 (no clinically significant insomnia), 8–14 (subclinical insomnia), 15–21 (moderate-to-severe insomnia).

##### 36-item short form health survey (SF-36)

2.8.3.2

Assessment timepoints: Consistent with the aforementioned schedule (T0-T2).

Health domains: Eight dimensions including physical functioning (PF) and role limitations due to physical health (RP).

Score transformation: Raw scores were converted to standardized scores (0–100) using the formula: [(Raw score - Minimum possible score)/(Maximum possible score - Minimum possible score)] × 100.

##### Inflammatory biomarkers

2.8.3.3

Assessment timepoints: Consistent with the aforementioned schedule (T0-T1).

Analytical method: Serum concentrations of IL-1*β*, IL-4, IL-6, TNF-*α*, hs-CRP, and TGF-β were quantified using enzyme-linked immunosorbent assay (ELISA).

Blood sampling protocol: Venous blood samples were collected at T0 (baseline) and T1 (post-intervention) under morning fasting conditions (≥8 h overnight fast).

Interpretation criteria: Concentrations were reported in pg/mL. Biological significance was defined as >15% change from baseline.

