### Sample size estimation

2.5

Based on existing RCT literature, the efficacy rate of taVNS in treating elderly patients with CI ranges from 73.3 to 93.3% (21, 22), while its efficacy in FD reaches 92.3% (3). Building upon our preliminary exploratory clinical study involving 10 cases, we observed an 80.0% efficacy rate (*p* < 0.01) for taVNS in treating elderly patients with CI comorbid with FD, demonstrating significant clinical effectiveness.

This study employed a superiority trial design and utilized PASS 2021 software (NCSS LLC, Kaysville, USA) for prospective sample size estimation. Based on clinical data reported in reference (23), with anticipated efficacy rates of 20% in the sham stimulation group and 70% in the active stimulation group, we conducted a two-independent proportion *z*-test analysis with the following parameters: type I error probability *α* = 0.05, statistical power 1-*β* = 0.99, and 1:1 allocation ratio. Through Monte Carlo simulation validation, the minimum theoretical sample size was calculated as 28 participants per group.

In accordance with CONSORT Statement guidelines regarding dropout rates and considering our institutional clinical practice experience with anticipated 5–10% dropout rates, we ultimately determined to enroll 30 participants per group (total *N* = 60). This sample size enables detection of a Cohen’s *h* effect size of 0.99 (Power = 0.991, 95% CI 0.89–1.07), satisfying the statistical power requirements for superiority trials.

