##### Neurotransmitter metabolomics profiling

2.8.3.4

Assessment timepoints: Consistent with the aforementioned schedule (T0-T1).

Analytical platform: Separation was performed using an Agilent 1,290 Infinity LC system coupled with a 5,500 QTRAP mass spectrometer (SCIEX) operated in negative ion mode.

Blood sampling protocol: Venous blood samples were collected at T0 (baseline) and T1 (post-intervention) under morning fasting conditions (≥8 h overnight fast).

Analytes:

Monoamines: DA, 5-HT, NE.Amino acids: Glu, GABA.

Interpretation criteria: Pearson correlation analysis was performed to assess the association between dynamic changes in neurotransmitter levels and improvement magnitudes of PSQI/NDSI scores, with |*r*| ≥ 0.3 defined as significant correlation (two-tailed test, *p* < 0.05).

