#### Statistical analysis

2.8.5

Primary analyses were conducted using the intention-to-treat (ITT) dataset, defined as the subset of participants who completed ≥1 intervention session, baseline assessment, and ≥ 1 post-baseline evaluation. In accordance with CONSORT guidelines, missing data were handled via multiple imputation (R package ‘mice’ v3.14.0). Sensitivity analyses were performed using the per-protocol set (PPS) to validate robustness.

The per-protocol set (PPS) followed ICH E9 guidelines with three integrated criteria: protocol compliance requiring 80–120% intervention dose completion, avoidance of prohibited medications, and key visit time deviations ≤3 days; data integrity enforcing <5% missingness in CDISC ODM v2.1-compliant CRF fields and laboratory CV% <15; and analytical scope restrictions that included cases with complete demographic/clinical data for baseline analysis, excluded efficacy cases with blinded-independent-adjudication-confirmed major protocol deviations (MPDs), while employing a modified PPS (mPPS) for safety analysis to retain participants discontinuing due to adverse events (AEs).

Post-trial, an independent third-party observer (uninvolved in study design or intervention delivery) performed the following: (1) Baseline data collection: Including gender, age, disease duration (months), BMI, education level, occupation category, marital status, and dietary patterns; (2) Outcome measures collection: Primary outcomes: Pittsburgh Sleep Quality Index (PSQI) and Nepean Dyspepsia Symptom Index (NDSI);Secondary outcomes: Insomnia Severity Index (ISI), 36-Item Short Form Health Survey (SF-36), inflammatory biomarkers (e.g., IL-6, CRP), and neurotransmitter levels (e.g., 5-HT, GABA); (3) Data de-identification: Removal of all direct or indirect identifiers (e.g., name, ID number), with assignment of unique study IDs.

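### The 15% biomarker rule has no comparator and sits at the tolerated assay CV, and the neurotransmitter correlation rule is not adjusted for arm, so neither isolates the mechanism claimed

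*Protocol article*

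**What the plan says.** Section 2.8.3.3 (Inflammatory biomarkers) covers six serum markers. "Venous blood samples were collected at T0 (baseline) and T1 (post-intervention) under morning fasting conditions", so each participant contributes two readings per marker. Its interpretation criterion is: "Biological significance was defined as >15% change from baseline". The section does not say whether a rise or a fall counts, whether the rule applies to a participant or to a group mean, or how the sham arm enters.

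Section 2.8.5 (Statistical analysis) lists "laboratory CV% <15" among the data-integrity conditions of the per-protocol set. It also plans two-sided between-group tests at 0.05.

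Section 2.8.3.4 (Neurotransmitter metabolomics profiling) uses Pearson correlation for the "association between dynamic changes in neurotransmitter levels and improvement magnitudes of PSQI/NDSI scores", with an absolute r "≥ 0.3 defined as significant correlation" alongside a two-tailed p below 0.05. Five analytes and two scales make ten pairs. The section does not say whether the arms are pooled or whether arm is adjusted for.

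On size, section 2.5 says: "we ultimately determined to enroll 30 participants per group".

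The abstract's discussion sets out to build an evidence chain linking efficacy, inflammation and neuromodulation.

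**The concern.** A change from baseline carries the error of two readings. A cut-off equal to the tolerated CV of one reading is therefore smaller than the standard deviation of the change that this imprecision alone produces. A criterion applied without the sham arm also gives up the protection of randomisation: drift in the assay, regression to the mean or a trend over three weeks can all meet it.

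The correlation rule has a different weakness. When two arms with different means are pooled, a correlation appears between any two variables that treatment shifts, whether or not they are related among participants treated alike. The rule is meant to show that neurotransmitter change goes with symptom improvement. Pooled, it may show only that both moved with treatment.

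At stake is the interpretation of secondary outcomes. They are not the primary endpoints, but they carry the mechanistic message of the article, and these are the only biomarker-specific interpretation criteria it gives.

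**Working it through.** The article gives no error rate for either rule, so there is no stated figure to reproduce.

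**Inputs from the article:** cut-off 15% and two readings per participant (2.8.3.3); CV ceiling 15% (2.8.5); absolute r of at least 0.3 with p < 0.05, and 5 × 2 = 10 pairs (2.8.3.4); 30 per arm, 60 in total (2.5). **Assumptions:** actual CVs of 5%, 10% and 15%; standardised treatment shifts; independence of the ten pairs.

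**1. The 15% rule per participant, no true change.** SD of change = √2 × CV. The probability of exceeding 15% in either direction is P(|Z| > 15 / (√2 × CV)).

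| CV | SD of change | 15 / SD | Probability |
|---|---|---|---|
| 15% | 21.2% | 0.71 | 48% |
| 10% | 14.1% | 1.06 | 29% |
| 5% | 7.1% | 2.12 | 3.4% |

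A log-normal simulation gave 47.4%, 28.6% and 3.5%. At CV 15%, a fall of more than 15% alone occurred in 22%. Day-to-day biological variation is not included.

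**2. The 15% rule on a mean of 30.** At CV 15% the standard error is 21.2 / √30 = 3.9%, and 15 / 3.9 is about 3.9. The probability is about 0.01% by the normal formula and 0.1% by log-normal simulation. Assay noise alone does not meet the rule on this reading. If within-person biological CVs of 20%, 30%, 40% or 50% are added (assumed; the article gives none), the geometric mean of one arm crosses 15% in 1.9%, 7.7%, 16% or 24% of null trials per marker.

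**3. Correlation cut-offs.** With t = r√((n−2)/(1−r²)), r = 0.3 gives p = 0.020 at n = 60 and p = 0.107 at n = 30. The r needed for p < 0.05 is 0.254 at n = 60 and 0.361 at n = 30. If both conditions must hold, 0.3 binds when arms are pooled and the p-value binds within an arm.

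**4. Pooled r with zero within-arm correlation.** With equal arms and between-arm shifts d1 and d2 in SD units, the expected pooled r is [d1/√(d1²+4)] × [d2/√(d2²+4)]. For equal shifts this is d²/(d²+4).

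| Shift in both | Expected pooled r | Pooled absolute r ≥ 0.3 (simulated, 30 per arm) |
|---|---|---|
| 1.0 SD | 1/5 = 0.20 | 21% |
| 1.3 SD | 1.69/5.69 = 0.30 | 52% |
| 1.5 SD | 2.25/6.25 = 0.36 | 73% |

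Setting d²/(d²+4) = 0.3 gives d = √(1.2/0.7) = 1.31. In the same simulations the arm-adjusted correlation reached 0.3 about 2% of the time. With no neurotransmitter shift, the pooled rate also stayed at about 2%, even with a score shift of 2 SD.

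**5. Ten pairs, all null.** Pooled, joint rule: 1 − (1 − 0.0199)^10 = 18%. Within one arm of 30: 1 − 0.95^10 = 40%. With 10% dropout (60 × 0.9 = 54 analysed), p at r = 0.3 is 0.0275 and the pooled figure becomes 24%.

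**The case against.** Several stronger readings are tempting, and the article does not support them.

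- A reader might infer that both rules can be met with no biological effect at all. That fails for the correlation rule: the arm-difference route needs a real treatment shift in the neurotransmitter, about 1.3 SD if both shifts are equal. What would be false is the link, not the effect. Nor can the needed shift be taken from the 70% and 20% response rates in section 2.5, which describe clinical response.
- A reader might take 48% as the error rate of the rule. It applies only per participant and at the CV ceiling. That ceiling is a per-protocol condition, and actual CVs may be lower. Assay noise also affects both arms alike, so it does not by itself create a between-arm difference.
- A reader might see the r and p cut-offs as contradictory. They can be read as a joint condition, a minimum size plus a significance test, which is coherent.
- A reader might apply the 40% to the pooled analysis. It belongs to the within-arm reading, where the arm-difference problem does not arise.
- A reader might infer that the mechanistic conclusion rests on these two rules alone. Section 2.8.5 also plans between-group tests, section 2.11.2 mentions regression adjusted for baseline covariates, and the Discussion calls the design exploratory.

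It is also fair to say that pooling and multiplicity for secondary correlations are often settled in an analysis plan, which is not shown. For that reason multiplicity is only a supporting point here.

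What remains is what the article itself fixes: a named criterion of biological significance with no level, direction or comparator, set at the assay tolerance, and a named correlation rule without arm adjustment. The planned between-group tests do not address whether neurotransmitter change accompanies symptom improvement.

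**Conclusion.** The point holds in a limited form. The 15% rule is not a sound criterion of effect on either reading. Per participant, 48% of unchanged participants meet it at CV 15%, falling to 3.4% at CV 5%. On group means assay noise is not the problem, but the rule still ignores sham and any time trend.

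The correlation rule, if arms are pooled, cannot separate a shared treatment shift from an association among participants. The size of this depends on an assumed neurotransmitter shift: expected r is 0.20 at 1.0 SD in both variables and about 0.3 at 1.3 SD. With no such shift, the false-positive rate is about 2% per pair. Over ten independent null pairs, the chance of at least one positive is about 18% pooled with 60 analysed, or about 40% within one arm of 30. Correlated pairs would change these two figures.

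A mistaken mechanistic claim is therefore possible, but these rules do not make it inevitable.

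**What to change.** **Section 2.8.3.3.** Drop the 15% rule as a criterion of effect. Base inference on the between-arm difference in T1 log-concentration, adjusted for log-baseline, with a 95% confidence interval. If an individual-change cut-off is kept, report it only descriptively, state its direction and derive it from observed variation. The value 1.96 × √2 × CV (41.6% at CV 15%, 27.7% at CV 10%) is a minimum, because it leaves out biological variation.

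**Section 2.8.3.4.** Replace the r cut-off with partial correlations adjusted for arm, each with a 95% confidence interval, and false-discovery-rate control over the ten pairs. Describe these as exploratory.

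**Cost.** Rewording of two sections and a little analysis, using data already collected. Fewer biomarkers and correlations will be reported as significant.

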##### Neurotransmitter metabolomics profiling

2.8.3.4

Assessment timepoints: Consistent with the aforementioned schedule (T0-T1).

Analytical platform: Separation was performed using an Agilent 1,290 Infinity LC system coupled with a 5,500 QTRAP mass spectrometer (SCIEX) operated in negative ion mode.

Blood sampling protocol: Venous blood samples were collected at T0 (baseline) and T1 (post-intervention) under morning fasting conditions (≥8 h overnight fast).

Analytes:

Monoamines: DA, 5-HT, NE.Amino acids: Glu, GABA.

Interpretation criteria: Pearson correlation analysis was performed to assess the association between dynamic changes in neurotransmitter levels and improvement magnitudes of PSQI/NDSI scores, with |*r*| ≥ 0.3 defined as significant correlation (two-tailed test, *p* < 0.05).

#### Blood sample processing

2.8.4

Venous blood was collected using 5 mL PET separator gel tubes with clot activator (Jiangsu Kangjian Medical Products Co., Cat.No. 0105–0512). Certified phlebotomists performed venipuncture between 08:00–09:00 under fasting conditions (≥8 h fasting), with blood volume strictly controlled at 5.0 ± 0.5 mL. Tubes were immediately labeled with subject-specific identifiers: unique study ID (STID), group allocation (A/B), and collection timestamp (YYYY-MM-DD HH:MM) on both tube body and cap. Samples were transported to the clinical laboratory within 10 min, allowed to clot at room temperature (22 ± 1°C) for 30 min, then centrifuged at 3,000 × g for 15 min at 4°C using a Shuke Benchtop Low-Speed Refrigerated Centrifuge (Sichuan Shuke Instrument Co., Model TDL-6). The supernatant was aliquoted into 2 mL cryovials (1.0 mL for inflammatory biomarkers and 2.0 mL for neurotransmitter profiling). All aliquots were flash-frozen in liquid nitrogen and stored at −80°C (Qingdao Haier Biomedical Co., Model DW-86 L828).

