**Methods/design:**

This double-blind randomized controlled trial will enroll 60 elderly patients (60–85 years) meeting ICSD-3 criteria for CI and Rome IV criteria for FD. Using block randomization with computer-generated sequences, eligible participants will be allocated 1:1 to either active taVNS group (*n* = 30) or sham control group (*n* = 30). The CFDA-certified transcutaneous vagus nerve stimulator (Model tVNS501, Reach Medical, China; Registration No. SuXieZhun20212090050) will be positioned at standardized anatomical sites: the concha cymba (the inferior margin of the intersection between the superior and inferior crura of the antihelix within the cymba conchae), electrical stimulation will deliver with fixed parameters (frequency: 80 Hz, pulse width: 100 μs, pulse 40–60s). The active group will receive validated taVNS parameters, while the sham group will undergo identical procedures without electrical output. Interventions will be administered 30 min per session, 5 sessions weekly for 3 consecutive weeks. Primary endpoints include changes in Pittsburgh Sleep Quality Index (PSQI) and Nepean Dyspepsia Symptom Index (NDSI) at week 3. Secondary outcomes encompass Insomnia Severity Index (ISI), 36-Item Short Form Survey (SF-36), and serum biomarkers (pro-inflammatory cytokines IL-1*β*, IL-4, IL-6, TNF-*α*, hs-CRP, TGF-β; neurotransmitters Dopamine (DA), serotonin (5-hydroxytryptamine, 5-HT), norepinephrine (NE), Glutamate (Glu), *γ*-aminobutyric acid (GABA)). Safety profiles will be systematically evaluated using CTCAE v5.0 criteria, with all adverse events documented throughout the study.

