### Randomization and blinding

2.6

The randomized controlled trial (RCT) utilized a simple randomization method implemented via the PROC PLAN procedure in SAS 9.4 software, which was designed by an independent statistician. A fixed seed number of 60 was preset to ensure reproducibility, and participants were allocated to the two groups (30 each) at a 1:1 ratio, with random numbering from 01 to 60, generating 60 unique sequences to ensure unbiased group allocation. The group allocation information was sealed in tamper-evident opaque envelopes and managed by a blinded study coordinator who was not involved in participant recruitment or outcome assessment, ensuring strict allocation concealment.

During trial execution, consecutively enrolled participants meeting inclusion criteria were sequentially assigned unique identification numbers. The blinded trial coordinator strictly adhered to the enrollment chronology when unsealing pre-sequenced, tamper-evident sealed envelopes. The revealed allocation information was subsequently transferred to an independent investigator uninvolved in recruitment or intervention delivery, who executed group assignments per the predefined randomization matrix. The study protocol explicitly prohibited any deviation from allocation sequences or non-programmatic modifications.

The independent researcher, based on randomized allocation, preset the transcutaneous auricular vagus nerve stimulator (tVNS501) with fixed parameters (intensity: 20–40 mA, frequency: 80 Hz, pulse width: 100 μs, pulse 40–60s) and blinded the display screen using opaque tape before handing it to a clinical operator. In the active stimulation group, the device was powered to deliver real stimulation, while in the sham stimulation group, the device remained inactive (no current output) but maintained physical contact. A triple-blind design (participant-operator-outcome assessor) was implemented throughout the study to maintain blinding of group assignment (taVNS or sham taVNS). Unblinding was performed post-database lock by an independent statistician using SAS 9.4 (SAS Institute Inc., Cary, NC), strictly adhering to the predefined protocol. This study strictly adhered to the principle of observer independence in clinical research (Figure 1).

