### Intervention

2.7

Following standardized screening, all participating clinicians underwent unified training in both taVNS and sham taVNS protocols. The informed consent form explicitly stated that the study involved two distinct neuromodulation interventions (which may differ in electrical sensation and therapeutic responses). Training modules included: (1) Device operation: standardized procedures for power cycling and locked parameter interfaces; (2) Anatomical localization: precise electrode placement at the tragus: the inferior margin of the intersection between the superior and inferior crura of the antihelix within the cymba conchae and the junction of the inferior crus of the antihelix and the auricle within the cymba conchae using auricular anatomical charts; (3) Blinding maintenance: standardized communication protocols to prevent unintentional disclosure of group allocation. All interventions were conducted in standardized treatment rooms within the hospital inpatient department.

All clinicians participating in this study were required to have at least 2 years of standardized acupuncture practice. Participants were placed in a supine position, and the auricular stimulation areas were cleaned with 75% ethanol solution followed by placement of ear clips. The clinically trained operator, blinded to group assignment, using transcutaneous auricular vagus nerve stimulators (tVNS501), precisely placed bipolar electrodes at standardized anatomical sites: the concha cymba (the inferior margin of the intersection between the superior and inferior crura of the antihelix within the cymba conchae). The intervention protocol consisted of 30-min sessions, administered weekdays from 9:00 to 11:00 AM for three consecutive weeks (15 sessions total).

Participants shall be withdrawn from the trial and provided with appropriate medical interventions under any of the following circumstances: (1) occurrence of serious adverse events; (2) voluntary withdrawal request from the participant; (3) clinical deterioration of the underlying condition; (4) requirement for prioritized treatment of other medical disorders; or (5) development of localized irritation or allergic reactions.

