#### Blinding implementation and outcome assessment

2.11.5

Blinding procedures mitigate measurement bias and expectation bias by preventing awareness of intervention assignments among investigators and participants. This study implemented a three-tier blinding system: (1) Participant blinding (using sham stimulation and blinded the display screen); (2) Investigator blinding (group allocation concealed via central randomization system); (3) Statistician blinding (de-identified raw data processing). Primary endpoints were assessed by an independent Endpoint Adjudication Committee using standardized scales (e.g., NIHSS scores) under blinded conditions, with committee members excluded from trial operations and denied access to allocation databases.

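### Group-coded blood tubes and a sham with no current undercut the claimed triple blinding; the first bears mainly on staff and biomarkers, the second on the participant-reported PSQI and NDSI

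*Protocol article*

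**What the plan says.** **Labels.** Under Blood sample processing (2.8.4), tube body and cap carry "unique study ID (STID), group allocation (A/B), and collection timestamp". The biomarker section (2.8.3.3) fixes when: "Venous blood samples were collected at T0 (baseline) and T1 (post-intervention) under morning fasting conditions". The baseline tube therefore already shows the group code.

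**Stimulation.** Randomization and blinding (2.6) presets the device at "intensity: 20–40 mA, frequency: 80 Hz, pulse width: 100 μs". In the sham arm "the device remained inactive (no current output) but maintained physical contact", and the abstract agrees: "the sham group will undergo identical procedures without electrical output". Intervention (2.7) gives 15 sessions of 30 minutes. It reports that the consent form describes two neuromodulation interventions "which may differ in electrical sensation and therapeutic responses".

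**Protection claimed.** Section 2.6 states triple blinding of participant, operator and assessor. The measures named are an independent person who presets the device, a taped display and sham contact (2.6), locked parameters and standardized communication (2.7), and concealed allocation and de-identified data (2.11.5). Section 2.11.5 adds that the primary endpoints are assessed by an "independent Endpoint Adjudication Committee using standardized scales (e.g., NIHSS scores) under blinded conditions".

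**Endpoints.** PSQI includes subjective sleep quality (2.8.2.1). NDSI covers symptoms such as early satiety and postprandial fullness (2.8.2.2).

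**The concern.** Double or triple blinding is a property of what people can see and feel, and here two stated procedures work against it.

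The label puts a fixed two-letter arm code in front of the staff who draw, transport and process blood. It serves no identification purpose, because the study ID already identifies the tube.

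The sham leaves a possible difference in sensation between the arms, and participants have been told to expect that such a difference may exist. These same participants supply the answers that make up both primary endpoints. If some of them infer their arm, part of any active–sham difference could be expectation. The Discussion plans to read superiority in both symptom domains as support for a neuroimmune mechanism, and its limitations paragraph does not mention this risk.

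**Working it through.** The plan gives no figure for blinding, so most of the check sets the sections side by side. The arithmetic at the end is illustrative.

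**1. Label against blinding.**
- 2.8.4 puts the A/B code on each tube; 2.6 claims operator and assessor blinding; 2.11.3 says allocation stays concealed until the intervention starts.
- A/B is not the arm name, but it is the same for everyone in an arm. One reliable link between a participant and an arm decodes every tube the same person sees.
- The people who see tubes are phlebotomists and laboratory staff. The outcomes within their reach are the cytokines and neurotransmitters, through clotting, centrifugation and aliquoting. PSQI and NDSI are affected only if the code travels on to participants or to those administering the scales.

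**2. Sham against participant blinding.**

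| Safeguard | Section | Masks presence or absence of sensation? |
|---|---|---|
| Taped display, preset device | 2.6 | No; hides settings |
| Electrode contact in sham | 2.6 | No; matches touch only |
| Locked parameters, communication rules | 2.7 | No; govern device handling and what staff disclose |
| Concealed allocation, de-identified data | 2.11.5 | No; act on staff and data |
| Adjudication committee | 2.11.5 | No; acts after the answers are given |

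The committee's example scale, NIHSS, appears nowhere among the outcomes in 2.8.2 and 2.8.3. A blinded committee cannot blind the person who answers a symptom questionnaire.

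**3. What bias of a given size would do (assumed range).**
Inputs from 2.5: 20% sham response, 30 per arm, α = 0.05; two-sided testing from 2.8.5. The plan's own 28 per group reproduces with unpooled variances: (1.960 + 2.326)² × (0.16 + 0.21) / 0.50² = 27.2, rounded up to 28. Nothing here disputes it.

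Assume no true effect, and let expectation raise reported active-arm response from 0.20 to p = 0.20 + b. With p̄ = (0.20 + p)/2, the chance of a significant result favouring taVNS is

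Φ{ [b√30 − 1.96√(2p̄(1 − p̄))] / √(0.16 + p(1 − p)) }.

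For b = 0.10: p̄ = 0.25, so (0.5477 − 1.96 × 0.6124) / 0.6083 = −1.073, and Φ = 14%.

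| b (assumed) | 0.05 | 0.10 | 0.15 | 0.20 |
|---|---|---|---|---|
| Chance (nominal 2.5%) | 6.7% | 14% | 25% | 39% |

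For a continuous score with a bias of d SD, the chance is Φ(d√15 − 1.96): about 12%, 21% and 49% for d = 0.2, 0.3 and 0.5.

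These are chances for one endpoint. Requiring both endpoints to be significant would lower them by an amount that depends on their correlation.

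**4. Precision of a blinding check.** Bang's index in one arm is the proportion guessing correctly minus the proportion guessing wrongly. If everyone guesses, its 95% half-width is 1.96√((1 − BI²)/30), which is 0.36 at BI = 0 and 0.31 at BI = 0.5. An index of 0.36 corresponds to (1 + 0.36)/2 = 68% correct, so only marked unblinding would stand out.

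**The case against.** Much can be said on the other side.

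- **The label does not by itself unblind the primary endpoints.** A reader might infer that one decoded participant unblinds all 60. The text does not support that. Decoding helps only someone who sees the tubes and also learns one participant's arm, and it tells the other 59 participants nothing. The assays are ELISA and mass spectrometry with computer printouts (2.8.3.3, 2.8.3.4, 2.11.6), which limits subjective influence. This stands, and it confines the label issue to staff and biomarkers.
- **The baseline label does not prove that concealment is broken.** A/B has no published key. Section 2.11.1 places concealment only up to enrolment, whereas 2.11.3 says up to the start of intervention. The article does not say how baseline sampling is ordered relative to randomization. The label sits badly with 2.11.3; more cannot be said.
- **Correct guessing by everyone is only a ceiling.** The article does not report how often the active setting is felt. Consent describes both arms as neuromodulation, and each participant experiences only one, so feeling nothing is not announced as sham. This is partly protective and stands. It does not remove the vulnerability, because the same text alerts participants to sensation as a possible difference.
- **The committee is not the only safeguard.** True, several are listed, but none masks sensation.
- **Absence of a blinding check.** A reader might conclude that the trial has none. Only a condensed article is at hand, so the most that can be said is that none is described there.

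**Conclusion.** The point holds in a limited form. The article's triple-blind claim is undercut by its own text in two places of unequal reach. The group code on tubes is an avoidable breach of staff blinding that matters chiefly for the secondary biomarkers. The sham without current, together with the consent wording, leaves participant blinding of PSQI and NDSI vulnerable, and the stated adjudication committee does not address that.

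The size of the resulting bias is unknown, because the documents give nothing from which to estimate it. The 7% to 39% range rests wholly on an assumed expectation gain of 5 to 20 points, no true effect, 20% sham response and 30 per arm. It shows that a modest bias would matter, not that one is present. It would be wrong to state as fact that the treatment effect is inflated, or that unblinding has occurred. That PSQI and NDSI are participant-reported is inferred from their described content; the article does not use that term.

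**What to change.** 1. Label tubes with study ID, visit and timestamp only. This is a template change at almost no cost.
2. Replace the committee and NIHSS statement in 2.11.5 with a plain description of PSQI and NDSI as participant-reported. This is a text correction.
3. Ask participants and operators to guess allocation after an early session and again at T1, before unblinding. Report a blinding index by arm beside the primary results. The early guess matters because a later one can also reflect felt benefit. State that the index has a half-width of about ±0.36 at 30 per arm, so a value near zero is weak reassurance. The cost is two short questions per participant, the same for operators, and any ethics notification this requires.
4. Add to the limitations, and to the conclusion if unblinding appears, that expectation effects cannot be excluded.

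None of these changes alters the sham itself; they limit the damage and make the risk visible. Rewording the consent is not requested: its present wording can be read either way, and a mid-trial change would need ethics review. Enrolment began in July 2024 (2.1), so the label change and the guess questions can apply only to remaining participants and samples. The text corrections and the limitation can be made in any case.
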